## Discussion

This study has been designed to achieve several outcomes: to collect necessary information to compare performance of BC evaluation criteria; to acquire necessary data to design stratified BC screening programs; to evaluate feasibility and impact of different screening strategies; to establish a conspicuous bio-bank useful to accurately validate selected biomarkers (and future novel ones) .

Although follow up is planned for 10 years, preliminary results will be available at the end of the three years of study duration. The above mentioned results could contribute in defining BC screening protocols on different risk factors other than age only, as it currently is.

Securely a critical aspect of the study could be represented by the acceptance of women to undergo a blood test. This point, though difficult, is a key point of the project as it will allow us to establish the bio-bank. To try and overcome these barriers and encourage women participation we are intensely working on communication and organization.

As concerns communication, very detailed information materials strongly emphasizing the goal of blood samples collection and its impact on the final outcomes of the study have been arranged. This material clearly explains the relevance of the personal history of each woman in terms of potential BC risk factors, so encouraging participants in following the whole study path.

The information material is designed to encourage, in a friendly and direct way, women to provide information about their lifestyle and a blood sample, so contributing to improve BC prevention strategies: a precious gift not only to themselves but also to other women.

Furthermore, a call centre has been be set up allowing women to get further information and to speak directly with a dedicated health operator. Particular attention is given to the training of health personnel interacting with women at the time of the screening, making them able to provide adequate and correct information. In particular, since the screening invitation letter is signed by GPs, they receive special educational interventions.

Regarding logistic aspects, we are giving participants the opportunity either to undergo blood drawing immediately after mammography or to fix a suitable appointment, facilitated by the fact that fasting is not necessary.

Particular attention is given to the formulation and administration of the LRQ, taking care to avoid overlap with the SRQ, reducing compilation times and trying to get standardized and comparable answers. The SRQ has been specifically designed for tablet devices to minimize both time and errors in inputting data.

Another concern is related to the molecular analyses. Since we do not know if specific miRNA levels fluctuate according to age or other demographical parameters or smoking exposure, we plan to use age and smoking matched patients without any diagnosis of (pre)malignant disease as controls for the miRNA analysis on plasma samples.

To face problems related to evaluation of miRNA expression particular caution is adopted especially regarding sample handling, timing and procedure of plasma separation, storage prior to extraction and protocols for RNA extraction and yield control. Our measures should be reliably translated in a screening context, therefore we analyze microRNAs already tested in prospective studies on plasma of cases before diagnosis and on matched controls, and validated using NGS approaches or Taqman on gene cards on independent cohorts.

A strength point of the study is represented by the prospective uniform nature of specimen collection for all subjects from a single cohort. This eliminates systematic biases by ensuring that case patients and control subjects are collected in exactly the same way and, in this case, from the setting for which biomarker is intended, that is the standard screening setting. Moreover, collecting and storing specimens before ascertaining the clinical diagnosis may provide information on the time dimension, that is, if the levels of the biomarker deviate from those in control subjects close to the time of clinical diagnosis, then the biomarker shows little promise for screening. On the other hand, if levels in case subjects reach levels distinct from those in controls years before clinical diagnosis, then the biomarker’s potential for early detection is increased.

Finally, the retrospective component of the design also avoids ethical problems, such as knowing the biomarker value without knowing how it should affect patient care. Moreover, sample storing will allow us future discovery, if more standardized and reliable techniques will become available, of novel circulating molecules whenever those selected will not satisfy our expectance.

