## Methods/Design

### Study aims

The Andromeda study was designed with two main aims: *1)* to define appropriate women risk-based stratifications for personalized screening considering different criteria such as: a model-based risk estimate of absolute BC risk including reproductive, BC family and biopsy history, breast density, lifestyle habits and *2)* to evaluate whether selected circulating miRNAs, previously associated to BC, are significantly altered in the plasma of cancer patients compared to matched healthy controls; and also if they satisfy pre-specified true and false positive rates, considered minimally acceptable in the screening setting.

In order to define groups of women characterized by different BC risk, the above mentioned criteria will be assessed and compared in terms of positive predictive value (PPV), either when considered alone or in combination. Related to the first main aim, secondary objectives are: to measure risk group-specific screening indicators (i.e., detection rate, recall rate and benign/malignant surgical biopsy ratio); to quantify the impact of tailored screening interventions on health outcomes; to evaluate the economic and organizational feasibility of these interventions.

With regards to the second main aim, secondary objectives are: to assess the tumor characteristics associated with miRNA levels in case subjects to understand the role of these biomarkers in cancer detection; to assess the association between the investigated BC risk factors and miRNA levels in the control group to define different thresholds for screening positivity; to evaluate the presence of 77 established SNPs associated with BC risk [18] and their impact on BC score calculation.

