**Fig. 1 Fig1:**
[figure not shown]
The Andromeda Study

Women who agree to participate in Andromeda are asked to fill in a short risk questionnaire (SRQ - Additional file 1) to collect information on general BC risk factors (reproductive and BC family history, previous breast biopsies, basic physical activity level, body mass index and alcohol consumption), immediately at the enrolment desk.

In addition, they are asked to fill in a long risk questionnaire (LRQ - Additional file 2) on diet, physical activity, smoking habits, general state of health and psychological distresses (sections on physical activity and on dietary habits were modified from the EPIC questionnaires [25], the section on psychological distresses was taken from the Brief COPE questionnaire [26]). Women are also invited to undergo anthropometric measurements (height, weight, body composition, and waist circumference) and to provide a blood sample for serum, plasma and buffy-coat storing. Blood specimens are aliquoted, processed and stored at −80 °C. These last procedures can be performed at the time of the examination or at a later date, to be agreed with the woman; fasting is not required.

Mammograms derive either from DM or from DBT (according to the Proteus trial randomization) and are read by two expert radiologists. Breast density is calculated during breast examination, through a specific algorithm [27] and it is classified into categories by means of the Breast Imaging Reporting and Data System (BI-RADS) [28].

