The sample size required with an 80% power (alpha = 5%) and assuming desirable true-positive rate and false-positive rate of TPR1 = 0.90 and FPR1 = 0.05, respectively, was of 179 cases and 537 controls. Sample size computation was based on theory on the Receiver Operating Characteristic (ROC) curve.

Assuming an annual BC detection rate (DR) of 0.006 in the first year and 0.005 in the second year of the study (therefore the biennial DR considered was 0.011) a total of 233 case patients in the first two years of the study are expected to be observed, thus exceeding the 179 required. These estimates are based on DRs observed in the previous years in the same centers considered in this study (Turin, Biella) [4]. Thus, the molecular analyses will be performed on 233 cases and 699 matched controls. For each case, three control subjects will be selected from the cohort of women, on the basis of the following criteria: no history of cancer, similar age at enrolment (within 5 years), similar race, availability of blood sample, similar date of blood draw.

Moreover, circulating miR-18a, miR-181a, and miR-222 levels - derived from the sister study cohort [21] - on plasma collected from all the women enrolled that have at least one first degree relative with BC will be assessed. The estimated number of this subgroup is 1800 women, 40 of which are expected to develop BC within 18 months, and will therefore belong to the case group.

To assess the predictive ability of the considered criteria (i.e., breast density, absolute risk of developing BC and, lifestyles) in identifying groups of women with different risk levels, the positive and negative predictive values and ratios of predictive values (PPV and PPV ratios) will be calculated for each criterion.

The discrimination ability of single biomarkers will be evaluated by means of the ROC curves, whereas to test if biomarker levels are significantly higher or lower in cases and controls, logistic regression models will be used. To evaluate the association between women’s characteristics or tumor features and biomarker level, linear regression models will be adopted.

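### Controls for the miRNA evaluation are defined in two different ways, and one of them excludes premalignant disease, so the false-positive rate tested against 4% may be understated for the screening population

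*Protocol article*

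**What the plan says.** The protocol article describes controls in three places.

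- Methods/Design, Statistical power and analysis: three controls per case from the cohort, on "no history of cancer, similar age at enrolment (within 5 years), similar race, availability of blood sample, similar date of blood draw".
- Discussion: "we plan to use age and smoking matched patients without any diagnosis of (pre)malignant disease as controls for the miRNA analysis".
- Study aims: markers are to be shown "significantly altered in the plasma of cancer patients compared to matched healthy controls", with no definition of healthy.

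The performance criterion is in Statistical power and analysis. The null hypothesis is a true-positive rate (TPR) of at most 0.80 or an FPR of at least 0.04, and the low FPR limit is justified by use in general population screening. The Discussion counts as a strength that cases and controls come "from the setting for which biomarker is intended, that is the standard screening setting".

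Smoking is collected in the "long risk questionnaire (LRQ - Additional file 2) on diet, physical activity, smoking habits, general state of health and psychological distresses". It is not among the items listed for the short questionnaire completed at the enrolment desk.

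**The concern.** The two rules give different control groups, and a reader cannot tell which one will supply the 699 controls. The difference in disease exclusion matters most. In a test for cancer, a woman with a premalignant lesion and no cancer counts as a non-case, and she is in the population the marker is meant for. If such women are dropped, the FPR is estimated in a cleaner group than the one to which the 4% limit refers. If the marker responds to early neoplastic change, the excluded women would be positive more often than the rest. The error then favours the marker on one of its two acceptance criteria.

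A second consequence is practical. Matching on smoking needs long-questionnaire data, while the Methods list asks only for a blood sample. Under the Discussion rule the pool of possible controls is smaller and is limited to women who completed the longer form.

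**Working it through.** **1. The two rules side by side**

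| Criterion | Statistical power and analysis | Discussion |
|---|---|---|
| Disease exclusion | history of cancer | any malignant or premalignant diagnosis |
| Age | within 5 years | matched, width not given |
| Race | similar | not named |
| Date of blood draw | similar | not named |
| Blood sample | must be available | not named, but implied by a plasma analysis |
| Smoking | not named | matched |

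No criterion in one column forbids a criterion in the other, but no sentence joins the two lists.

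**2. The plan's own figures**

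The ratio of three controls per case is kept throughout: 3 × 179 = 537 and 3 × 233 = 699. The 179 cases can be approximated with a fixed-FPR ROC formula, n = (z_a√V0 + z_b√V1)² / (TPR1 − TPR0)², where V = TPR(1 − TPR) + r²·f(1 − f)/3. Take f = 0.05, two-sided alpha 0.05, 80% power and equal-variance binormal slopes r of 2.715 at TPR 0.80 and 1.702 at TPR 0.90. The slopes are an assumption, and other variants come close.

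- V0 = 0.160 + 0.117 = 0.277 and V1 = 0.090 + 0.046 = 0.136.
- n = (1.960 × 0.526 + 0.842 × 0.369)² / 0.01 = 179.9, against 179 stated.

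Neither control rule enters this formula, so the sample size is unaffected.

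**3. Effect of the exclusion on the FPR**

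Let F be the FPR in all non-cancer women, p the share of them with a premalignant diagnosis, and q the share of those who are marker-positive. The FPR in the remaining women is

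F_restricted = (F − p·q) / (1 − p).

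F = 0.04 is the article's limit and 699 is its number of controls. The values of p and q are assumptions, because the article gives neither.

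The FPR component is tested here by a one-sided exact binomial test at a nominal 5%. With 699 controls and a true FPR of 4%, P(X ≤ 19) = 0.045 and P(X ≤ 20) = 0.070, so the test rejects at 19 positives or fewer and its actual size is 4.5%.

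| p | q | F_restricted | P(X ≤ 19) |
|---|---|---|---|
| 1% or 2% | 4% | 0.0400 | 4.5% |
| 1% | 20% | (0.04 − 0.002)/0.99 = 0.0384 | 6.9% |
| 2% | 20% | (0.04 − 0.004)/0.98 = 0.0367 | 10.3% |
| 1% | 50% | (0.04 − 0.005)/0.99 = 0.0354 | 14.1% |
| 2% | 50% | (0.04 − 0.010)/0.98 = 0.0306 | 34.9% |

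The null hypothesis is a union (TPR too low or FPR too high), so rejection needs both components to succeed. The joint rejection probability cannot exceed the FPR component's probability, and each figure in the last column is therefore an upper bound for the joint test.

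**4. The same effect in the other direction**

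If the restricted controls show exactly 4%, the FPR in all non-cancer women is (1 − p) × 0.04 + p·q. With p = 1% and q = 20% this is 0.0396 + 0.002 = 4.16%. With p = 10% and q = 40% it is 0.036 + 0.040 = 7.6%. With q = 4% it stays at 4%.

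**The case against.** The strongest defence is that the two lists are compatible. The Discussion sentence is a remark about confounding of miRNA levels, the Methods list is the operative rule, and both could be applied together. That is fair, and calling the rules mutually exclusive would go too far. What stands is that the article never says they are combined. Combining them would also keep the premalignant exclusion.

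A second defence is that the bias is conditional. This also stands. If women with premalignant disease are positive no more often than others, nothing is distorted; if they are positive less often, the FPR is overstated. The 35% figure needs a positivity of 50%, which is 12.5 times the 4% background and has no support in the article. It also concerns the FPR component alone. It is the top of an assumed range, not the error rate of the planned test.

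A reader might also infer that the matched data will be analysed as if unmatched. The article says "to test if biomarker levels are significantly higher or lower in cases and controls, logistic regression models will be used" and "The discrimination ability of single biomarkers will be evaluated by means of the ROC curves", and does not mention the matched sets. The documents do not support that inference. Conditional logistic regression is a logistic regression model, and a condensed article may leave conditioning, covariates and adjusted ROC curves to an analysis plan that is not shown. Attenuation would also require the markers to vary with the matching factors, and the authors write that "we do not know if specific miRNA levels fluctuate according to age or other demographical parameters or smoking exposure". In simulation with 233 sets of 1:3 and a true log odds ratio of 1.0, an unmatched analysis showed no attenuation when the marker was unrelated to the matching factor. When they were related, adjusting for the factor removed the attenuation as well as conditioning did.

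**Conclusion.** The point holds in a limited form. That the article gives two different control definitions is certain from the text. That excluding premalignant disease moves the control group away from the stated screening target follows directly. That the FPR is understated is possible but not shown: it requires these women to be marker-positive more often than other non-cancer women. At 1–2% prevalence, the FPR component's false rejection rate goes from 4.5% with no difference to 7–10% at 20% positivity and 14–35% at 50%, and these are upper limits for the joint test. The rule should be settled before controls are drawn. No claim is made that the regression or ROC analysis is wrong, or that the sample size is affected.

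**What to change.** 1. State a single control rule in one place, listing every exclusion and matching factor, and make the Methods, the Discussion and the description of controls in the aims agree with it.
2. Keep women with premalignant but non-cancer findings among the controls used for FPR and ROC. Alternatively, report FPR with and without them, and restrict the claim about the 4% limit to the population actually sampled.
3. If smoking remains a matching factor, say that eligible controls are then limited to women with long-questionnaire data, and report how many are lost for that reason.

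The cost is a change of wording made before control selection, with no increase in the planned 699 controls. The downside is that the observed FPR may look slightly worse.

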## Abbreviations

BC: Breast cancer
BS: Blood sample
DBT: digital breast tomosynthesis
DM: Digital mammography
DR: Detection rate
FPR: False positive rate
LRQ: Long risk questionnaire
MiRNA: microRNA
PCR: Polymerase chain reaction
PPV: Positive predictive value
PRoBE: Prospective specimen collection plus retrospective blinded-evaluation
R: Randomization
ROC: Receiver operating characteristic curve
SNP: Single-nucleotide polymorphism
SRQ: Short risk questionnaire
TPR: True positive rate
